### Assessment and outcomes

#### Oslo Sports Trauma Research Centre Questionnaire on Health Problems

The Oslo Sports Trauma Research Centre Questionnaire on Health Problems (OSTRC) is a tool to capture and monitor health problems longitudinally in athletes. It consists of 18 questions, which are answered for the past 7 days. The first four questions are to determine the severity of the health problem, while the rest are to further classify the health problem, such as type and anatomical location of the problem.^40^ As per previously established protocol, the athletes in our study will self-report their health status weekly with the help of a physiotherapist, while using the OSTRC questionnaire.^40^ The athletes with reported health problem will be contacted by a medical professional to clinically verify the reported health case.

#### Life Events Survey for Collegiate Athletes Questionnaire

At the baseline and final measurements, the athletes will be asked to complete Life Events Survey for Collegiate Athletes (LESCA)^41^ in order to get more contextualised view of the life events that were happening in the past 12 months. LESCA is a 69-item questionnaire where athletes rate how each life event affected their lives in the past 12 months on a −4 to 4-point scale (−4, extremely negative to +4, extremely positive). The events include personal, academic-related and sports-related events. From summing the rated life events, two life stress scores, negative (NEG) and positive (POS) are obtained, while a total life stress score can as well be obtained by summing the NEG and POS scores together.^41^

#### Weekly load and stress questionnaire

The teams will weekly report training and competition load for each athlete, while academic (educational activities, including lectures, exams and studying) and work load (a part-time or full-time job besides playing sports) for the past 7 days will be reported by the athletes themselves. Competition load will be reported in minutes for each game played in the past week, while training, academic and workload will be reported in hours. The athletes will additionally report average hours slept per day over the past week and rate their perceived overall stress of that week on the scale 1–10.

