### Statistical analysis

Statistical analysis will be performed using standard statistical software (SPSS V.27.0, IBM, Armonk, New York). Descriptive statistics will be used for all variables. Normality of data distribution will be assessed using the Shapiro-Wilk test. In case of non-normally distributed data, non-parametric statistics will be used, otherwise, the statistics for normally distributed data will be used. The data will be analysed using a logistic regression model to properly account for the dependency induced by the repeated observations over time within each subject. Main effect of all dependent variables on injury/illness occurrence will be studied using repeated measures analysis of variance (ANOVA) with time (preparation period vs competition period vs off-season period) as within factor, while group (injured/ill vs healthy) as between factor. Where significant effects will be found for group, time effects or two-way interactions, pairwise comparisons will be used to address the significant differences for each variable independently. For comparison of the groups, we will use independent t-test. The magnitude of effect for all dependent variables will be reported as partial eta squared (η^2^). In addition, *Cohens’ d* (ES) will be used to assess magnitude of difference between groups. Furthermore, regression analysis will be used to assess predictive power of individual parameters to identify injury/illness occurrence. For the correlation of subjective measures of stress with the objective measures, bivariate correlation will be used. Additionally, Bland-Altmann analysis will be used (low/high stress normative values) as previously recommended.^42^ Furthermore, receiver operating characteristic (ROC) curve analysis will be used for defining the cut-off values. Hypotheses will be accepted or rejected at p≤0.05.

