### Patient and public involvement

Patients and/or the public were not involved in the design and/or conduct, and/or reporting of this study. The project results will be presented to the participants in collaboration with the team staff (strength and conditioning coaches, physiotherapists, kinesiologists, etc). Furthermore, the participants of the proposed study will be invited to share their experiences of their involvement in our project with elite athletes playing other sports in the Republic of Slovenia in order to continue to implement ‘good practice’ with future projects.

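### Training and competition load are reported team by team, but none of the named analyses has a club term, so a club-level factor behind both recorded load and recorded health problems would appear as a load effect

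*Protocol article*

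**What the plan says.** Under Weekly load and stress questionnaire, the source of the physical-load data is the team: "The teams will weekly report training and competition load for each athlete". Academic and work load "for the past 7 days will be reported by the athletes themselves", and sleep and perceived stress also come from the athlete.

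Under the section on the Oslo health-problems questionnaire, athletes "will self-report their health status weekly with the help of a physiotherapist, while using the OSTRC questionnaire". The physiotherapist's employer is not stated. Verification follows a positive report: "The athletes with reported health problem will be contacted by a medical professional to clinically verify the reported health case".

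Under Statistical analysis, a logistic regression is to be used "to properly account for the dependency induced by the repeated observations over time within each subject". The section also names a repeated-measures ANOVA with injured/ill versus healthy as the between factor, independent t-tests between the groups, further regression, correlation, Bland-Altman analysis and ROC cut-offs. The player is the only level of dependency mentioned. No analysis is stratified by, adjusted for or clustered on club.

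**The concern.** All players come from the clubs of one league. If team-mates train on a common programme, recorded hours differ between clubs as well as between players and weeks. Clubs may also differ in how completely they report, in medical care and in playing level. If one such factor raises or lowers both the recorded hours and the recorded health problems, a comparison that pools players across clubs will attribute the club difference to load.

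This is a bias in the estimate. Widening the standard error to allow for correlation within players or clubs leaves the estimate where it was. At stake is the physical-load part of the primary aim, including any load cut-off offered to practitioners.

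**Working it through.** **The plan's own figures.** The article gives no figure for club effects. Its dropout step reproduces: 134/(1 − 0.10) = 148.9, rounded up to 149. No club allowance enters that calculation.

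**Step 1: which named analyses use between-club differences.**

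| Analysis | Comparison used | Exposed? |
|---|---|---|
| Independent t-test | injured/ill vs healthy players, all clubs pooled | yes |
| ANOVA group factor | same | yes |
| ROC cut-offs | same | yes |
| Logistic model, marginal or random-intercept | mixture of between- and within-player | yes |
| Logistic model, conditional or purely within-player | each player against himself | no, for stable club differences |

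The article does not say which form the logistic model takes.

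**Step 2: approximate size of the bias.** Let one SD of a club factor add *a* hours to recorded weekly load. Let one SD of a second club factor add *g* to the log-odds of a recorded problem, and let the two factors correlate at *r*. With no true load effect, the pooled slope per hour is roughly

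slope ≈ r·a·g / Var(load).

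Assumed SDs of load, none of them in the article: other club differences 0 to 2 h, players 1 h, weeks 2.5 h. Then Var(load) = a² + (0 to 4) + 1 + 6.25.

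- Lower setting, a = 0.5, g = 0.2, r = 1: 0.10/7.5 to 0.10/11.5 = 0.0133 to 0.0087 per hour. Over 5 h the OR is exp(0.067) to exp(0.043), or 1.07 to 1.04.
- Upper setting, a = 1, g = 0.4, r = 1: 0.40/8.25 to 0.40/12.25 = 0.0485 to 0.0327 per hour. Over 5 h the OR is exp(0.242) to exp(0.163), or 1.27 to 1.18.
- r = 0: slope 0, so no bias.

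**Step 3: simulation of the same settings.** Assumed: 12 clubs × 12 players × 40 weeks, no true load effect, player-clustered standard errors. Two sets of runs gave the ranges below. The ORs are from the set that used the load SDs in Step 2.

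| Correlation r | Setting | OR per 5 h | Significant at 5% |
|---|---|---|---|
| 1 | lower | about 1.05 | 9–12% |
| 1 | upper | 1.15–1.22 | 47–66% |
| 0.5 | both | 1.02–1.09 | 6–29% |
| 0 | both | no bias | 6–20% |

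With club as a fixed factor, 1–9% were significant. The excess at r = 0 is not bias. It arises because player-clustered errors ignore club: at the upper setting, 16–20% fell to 7–8% with club-clustered errors.

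**Step 4: a different mechanism, incomplete reporting.** Assumed: 14 clubs × 11 players, about 20% weekly prevalence, and one completeness level per club, uniform over a range and shared by load and health reports. The 46 weeks are from the article. There were 1000 runs per row and no true load effect.

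| Completeness: load / health | Pooled, player-robust SE | Pooled, club-robust SE | Club fixed factor |
|---|---|---|---|
| no club differences | 5.7% | 6.8% | 5.7% |
| 90–100% / 80–100% | 5.6% | 7.6% | 6.2% |
| 80–100% / 60–100% | 12.1% | 14.1% | 5.3% |
| 70–100% / 50–100% | 34.4% | 33.7% | 5.1% |

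With 10 clubs × 15 players, the third row gave 12.5% pooled and 5.8% with a club factor. With load and health completeness independent across clubs, the pooled rate in that row was 5.9%. The purely between-player component reached 49% false positives and a mean OR of 1.27 per pooled SD of load in the last row. The purely within-player component stayed at 3.9–7.3% throughout.

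**The case against.** The strongest reply is that the article lists no covariates at all, not even age, position or previous injury, which it collects. Silence in a condensed article is not a decision to pool across clubs, and the full protocol or SAP may hold a club term. This stands as far as the logistic model goes. It does not cover the analyses the article does name: an unadjusted two-group t-test and an ANOVA group factor compare different players across clubs as written.

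A reader might infer that clubs record both load and health problems. The documents do not support that. Health is self-reported, the physiotherapist's employer is not given, and the only mention of physiotherapists as team staff concerns presenting results to participants. Nor does anything in the article show that a club that logs fully also elicits more complaints. If the two are unrelated, there is no bias. Clinical verification does not settle the matter either way, since it reaches only reported problems and cannot recover missed ones.

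A reader might also infer that every analysis is biased. A within-player logistic model would not be, and the stated aim of learning how much variation in an athlete's load precedes a problem can be read that way.

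Finally, the primary aim covers physical, psychosocial and dual-career loads together, and the sample size rests on academic stress. The team-recording route reaches training and competition load only.

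**Conclusion.** The point holds in conditional form. What the article establishes is team-reported training and competition load, named between-player comparisons and no club term. What it does not establish is that a shared club factor is present, or how strong it is.

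The size therefore has to be given as a range: about 6% false positives if club differences are mild or weakly correlated, 12–34% under moderate to strong shared incompleteness, and roughly 50–65% when strong differences are fully shared. The top of that range should not be read as the expected error rate. It needs a correlation of 1 between the club effects on load and on health reports, and it includes some under-clustering. The number of clubs, the spread of load and the reporting differences are all assumed.

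Under both mechanisms, comparing players within clubs brought the rate back to near 5%, whereas club-clustered errors did not help against shared incompleteness. This is a worthwhile, inexpensive improvement. It does not show that the planned result is wrong.

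**What to change.** State the form of the weekly logistic model. Unless it is purely within-player, add club as a fixed factor, so that load is compared among players and weeks of the same club. Report the training- and competition-load estimates with and without it. If the ANOVA and t-tests are kept, run them for these two loads on values centred within club.

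Cost: club is already known for every player, so no new data are needed. The model spends about one degree of freedom per club, and the interval widens somewhat because between-club variation in load is no longer used. Changes over time in a club's reporting are not removed. If the two estimates agree, the load result is stronger for it; if they differ, readers need to see both.

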**Figure 1 F1:**
[figure not shown]
Assessment plan. LESCA, Life Events Survey for Collegiate Athletes.

**Table 1 T1:** Questionnaires and tests

Test/questionnaire	Outcome	Purpose
**SDSCQ**	Age, sex, level of education, sport, years of training, player position, previous injuries	General information about the athlete
**Anthropometry**	Body height (cm), body weight (kg)	Measure of basic anthropometric characteristics of an athlete
**LESCA**	Major life events score	Measure of life stress
**OSTRC**	Weekly health problems (acute and overuse injuries, illnesses), measured as prevalence and incidence and severity as OSTRC-severity score and time-loss days	Identifying health problems
**Weekly load and stress**		Monitoring of athlete’s load
	Training load in hours	
	Competition load in minutes	
	Academic load in hours	
	Work load in hours	
	Average daily sleeping hours	
	Perceived stress on scale 1–10	
**Blood biomarkers**		Monitoring of stress/insufficient recovery and/or health problem risk
Cortisol	Cortisol values in nmol/L	
Free testosterone	Free testosterone values in pmol/L	
Ig-A	Ig-A values in g/L	
	Free testosterone: cortisol ratio	

LESCA, Life Events Survey for Collegiate Athletes; OSTRC, Oslo Sports Trauma Research Center Questionnaire on Health Problems; SDSCQ, Sociodemographic and Sports-Career Related Questionnaire.

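### Load, sleep, stress and health problems share one recall week, and no stated analysis places exposure before onset, so the load associations can be biased in either direction

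*Protocol article*

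**What the plan says.** All places are in the protocol article.

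- **Outcome.** The section on the Oslo questionnaire says: "It consists of 18 questions, which are answered for the past 7 days". Table 1 lists the outcome as "Weekly health problems (acute and overuse injuries, illnesses), measured as prevalence and incidence", with severity that includes time-loss days.
- **Exposures.** In the section Weekly load and stress questionnaire, academic and work load "for the past 7 days will be reported by the athletes themselves". For the club's part, "The teams will weekly report training and competition load for each athlete"; "Competition load will be reported in minutes for each game played in the past week". Athletes also give "average hours slept per day over the past week and rate their perceived overall stress of that week".
- **Life events.** LESCA is completed at baseline and at the end "in order to get more contextualised view of the life events that were happening in the past 12 months".
- **Analysis.** The Statistical analysis section names a logistic model for repeated observations; a repeated measures ANOVA with season period as within factor and injured/ill against healthy as between factor; t-tests between groups; ROC curves for cut-offs; and a further step in which "regression analysis will be used to assess predictive power of individual parameters to identify injury/illness occurrence". It mentions no lag, onset date or restriction to new problems in players at risk.
- **Aim.** The end of the Introduction asks a directional question: how loads affect injury and illness, and how much variation in load results in one.

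**The concern.** A player hurt early in a week trains and plays less in the rest of it, may sleep worse and may report more stress. The form for that week then pairs a health problem with low training load, short sleep and high stress, whatever came before the injury. A same-week association therefore blends the effect of load on injury with the effect of injury on load.

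The group-by-period comparison has the same fault over a longer span: an injured player's average for the competition period includes the weeks missed because of the injury. At stake are the answer to the primary aim and the ROC cut-offs. A load cut-off derived from such data could make high training load look safer than it is.

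**Working it through.** **1. Windows side by side.** Health problems: past 7 days. Academic and work load: past 7 days. Competition load and sleep: past week. Stress: that week. Training load: reported weekly by the teams, which I read as the same week. Exposure and outcome share one window.

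**2. Time order in each analysis.** The period ANOVA and the t-tests average load over spans that contain both pre-onset and post-onset weeks, so they are unordered by construction. For the logistic, predictive and ROC analyses the article does not say how weeks are aligned.

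**3. Size for training load.** The plan gives no figure for this bias. Taken from the documents: 149 players (134/(1-0.10) = 148.9, rounded up) and 46 weeks. Assumed, because the documents are silent: mean load m = 10 h/week, SD s = 2.5 h, weekly risk of a new problem 2% to 5%, mean duration 1 to 3 weeks, onset uniform within the week, and a fractional cut c in load after onset.

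Let b be the true log OR per SD. With a rare outcome and normal load, players with an onset have mean planned load m + b·s. With onset at a uniform time, half the week is affected on average, so observed load is (m + b·s)(1 - c/2). The same-week log OR per SD is then approximately

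b - (c/2)(m/s + b).

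For a true OR of 1.50, b = 0.405, m/s = 4 and the bracket is 4.405. The last two columns are simulated (149 players, 46 weeks, 30 to 40 replicates per scenario).

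| Cut c | Approximate log OR | Approximate OR | Simulated OR, new onsets | Simulated OR, prevalent problems (mean 3 weeks) |
|---|---|---|---|---|
| 0% | 0.405 | 1.50 | 1.47-1.53 | 1.17-1.34 |
| 10% | 0.405 - 0.220 = 0.185 | 1.20 | 1.21-1.23 | 0.83-0.93 |
| 25% | 0.405 - 0.551 = -0.146 | 0.86 | 0.84-0.88 | 0.47-0.54 |
| 50% | 0.405 - 1.101 = -0.696 | 0.50 | 0.48-0.51 | 0.18-0.20 |

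The approximate OR for new onsets crosses 1 at c = 2 × 0.405/4.405 = 18%. With no true effect and a 25% cut, the approximation is exp(-0.5) = 0.61 and the simulated OR is 0.59 for new onsets and 0.40 for prevalent problems.

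**4. Period comparison, true OR 1.50, mean duration 3 weeks.** With no stable load differences between players, a 25% cut makes injured players average 0.25 to 0.36 h/week less load than healthy ones. If half the load variance is stable between players, the contrast is +0.65 to +0.90 h/week with no cut, +0.35 to +0.49 at 25% and +0.06 to +0.09 at 50%: it shrinks but does not reverse.

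**5. What repairs it.** If the previous week's load carries a true OR of 1.50, a one-week lag with new onsets in problem-free players returns 1.47 to 1.51 at any cut from 0% to 100%. A lag with prevalent problems does not repair it: 0.69 to 0.77 at a 25% cut. If the effect acts within the same week and load varies independently from week to week, the lagged onset OR is 0.98 to 1.00, so a lag alone misses it.

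**6. Other exposures.** This is reasoning only. Injury can raise stress and disturb sleep, which would make high stress and short sleep look more harmful. An injured player may study or work more or less, so the sign for academic and work load cannot be given.

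**The case against.** The strongest reply is that this is a condensed article. Lag structure and risk set are commonly left to an analysis plan, weekly serial reports are exactly what makes a lag possible, and incidence is already among the listed measures. Much of that stands. A reader might infer that the logistic model will be run without a lag; the article is silent on this and does not say so. Nor is the shared recall week itself a fault in data collection.

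A reader might also infer that a harmful load will appear protective. The documents do not support that as a general statement. It can apply only to training and competition load, and it depends on a load loss that they do not report: at a 10% cut and a true OR of 1.50 the onset OR is only attenuated. The magnitudes largely restate the assumed cut. With m/s = 4, a 25% cut after onset is a mean loss of half an SD.

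A third inference would be that the final LESCA, which looks back over the season, is to be used as a predictor of problems in that season. The article gives its purpose as context, and a baseline LESCA is collected.

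The reply does not reach the group-by-period ANOVA and t-tests. They are stated, and they lack time order by construction. It also does not remove the need for time order in the regression and ROC analyses, since the primary question is about what comes before injury.

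**Conclusion.** The point holds in this form: exposure and outcome share a week, two stated analyses mix load before and after onset, and the others do not say that exposure comes first. Followed as written, the plan can bias the primary answer.

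For training and competition load the bias runs towards or past the null. Under the assumptions above, a true same-week OR of 1.50 per SD appears as about 1.2 at a 10% cut and about 0.85 at a 25% cut, and lower still if prevalent problems are the outcome. Whether the sign reverses in this cohort cannot be settled from the documents. For stress and sleep the bias more likely exaggerates harm. For academic load, on which the sample size rests, and for work load, the direction is unclear.

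**What to change.** - Make the primary load analysis a repeated-measures logistic model of new health problems in week t among athletes problem-free at the end of week t-1.
- Take exposures from before onset: week t-1 and a rolling mean of prior weeks, plus pre-onset load within week t where the onset date is known.
- Derive the ROC cut-offs from these exposures.
- Report same-week associations, and the injured-against-healthy period ANOVA and t-tests, as descriptive only.
- If LESCA is used to predict in-season problems, use the baseline score only.

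Most of this is analysis wording on data already collected. Each athlete's first week and all weeks with an ongoing problem leave the risk set. A one-week lag alone can miss effects acting within the week, hence the pre-onset term; that term needs onset dates, and training hours kept only as weekly totals cannot be split at onset.

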#### Blood biomarkers

There will be three to five measurement timepoints for biomarker sampling, according to the training (preparatory period, competitive period, off-season period) cycle. The athletes will be tested under similar conditions every time, after a rest day (refrainment from intensive training the day before blood collection), between 7:00 and 10:00 in the morning.

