### Biomarkers

Biomarker discovery and validation is a critical aim of the medical and scientific community.^33^ Biomarkers can be used as an objective assessment tool for health, performance, recovery and talent identification in elite sport. Among the most critical hormones for athletes seem to be cortisol, testosterone, dehydroepiandrosterone and immunoglobulin-A (Ig-A). However, testosterone to cortisol (T:C) ratio is considered to be more sensitive to training stress than either measure alone,^33^ as several studies report poor performance outcomes and suboptimal training adaptations in athletes with a low T:C ratio.^34 35^ However, to the best of the authors’ knowledge, no previous work has examined the use of biomarkers for injury prevention, recovery after an injury or identification of individuals at increased risk.

Given all of the above, there is a need for better health surveillance, load monitoring and support services with an emphasis on injury/illness prevention and rehabilitation.^36^ As DC athletes have a wider variety of loads that pose greater psychophysiological strain to them, they could also be at an increased risk for injury/illness. Therefore, more comprehensive monitoring of potential risk factors in this specific population is warranted. It is not yet known, but important to determine how much of overall load can an athlete withstand before injury/illness occurs. Thus, the primary aim of this study is to determine how specific physical, psychosocial and DC loads affect the occurrence of injuries and illnesses in elite handball players and how much of a variation in the athlete’s load leads to an occurrence of an injury/illness. A secondary aim is to determine the association between objective and subjective measures of stress as well as examine the benefits of certain biomarkers to monitor stress, load and injury/illness occurrence in athletes.

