## Methods and analysis

### Study design

The study is designed as a prospective cohort study. All measurements will be conducted over a single handball season, lasting from July 2022 to June 2023 (a total of 46 weeks), with weekly reporting (table 1) and three to five biomarker sampling timepoints (figure 1). We used the Standard Protocol Items: Recommendations for Interventional Trials (SPIRIT) checklist when writing our report.^37^

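### The biomarker analyses do not place blood draws before health problems in time, so three to five draws in 46 weeks cannot support short-lead prediction of most onsets

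*Protocol article*

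**What the plan says.** The secondary aim, at the end of the Introduction, includes the intention to "examine the benefits of certain biomarkers to monitor stress, load and injury/illness occurrence in athletes". Table 1 gives the purpose of the blood biomarkers as "Monitoring of stress/insufficient recovery and/or health problem risk".

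The two data streams run at different rates. Under Study design the season is described as "lasting from July 2022 to June 2023 (a total of 46 weeks), with weekly reporting". In the OSTRC section, "the athletes in our study will self-report their health status weekly with the help of a physiotherapist". For blood, the Blood biomarkers section states: "There will be three to five measurement timepoints for biomarker sampling, according to the training (preparatory period, competitive period, off-season period) cycle".

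The Statistical analysis section then plans:
- a logistic regression that allows for repeated observations within a player, with no statement of how a biomarker value enters it;
- a repeated measures ANOVA "with time (preparation period vs competition period vs off-season period) as within factor, while group (injured/ill vs healthy) as between factor";
- a further regression: "regression analysis will be used to assess predictive power of individual parameters to identify injury/illness occurrence";
- ROC curves to define cut-off values.

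The text gives no interval between a blood draw and the health problem it is set against, and no rule on which comes first.

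**The concern.** Monitoring health problem risk is a claim about what follows a blood value. To test it, the value must precede the problem, and the time over which it is meant to be informative must be stated.

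The ANOVA does neither. A between-subject factor gives each player one label for all his draws. A player hurt late in the season counts as injured for a preparatory-period draw taken months before, and a player hurt early counts as injured for draws taken long after. A difference between groups could then be a forerunner of the problem or its result, through lost training, pain or treatment. A null result could come from averaging over draws far from any event. The later regression and the ROC curves do not repair this as written, because no time order is given for them either.

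At stake is a published cut-off for cortisol, free testosterone, Ig-A or the testosterone to cortisol ratio that has no time horizon and may partly describe players who were already hurt or ill. The article's strengths and limitations list claims direct implications for practice and prevention, so such a cut-off could be used.

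**Working it through.** The protocol gives no figure for the biomarker aim that could be reproduced. Its sample size (134, raised to 134/0.90 = 149) is for academic stress and injury and does not bear on this point.

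**Inputs from the article.** Follow-up W = 46 weeks (Study design). Number of draws k = 3 to 5 (Blood biomarkers). Players N = 149 (Participants and sample size) to 200 (Abstract). Prevalence of health problems 20% to 45% (Introduction, as cited background).

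**Assumptions, not in the article.** Draws evenly spaced with the first at season start; onsets spread evenly over the season; where event counts are needed, 2% to 10% new problems per player-week.

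**Step 1: distance from draw to onset.** Gap = W/k. Mean lag from latest draw to onset = W/(2k). Share of onsets more than w weeks after the latest draw = 1 − kw/W.

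| Draws | Gap (weeks) | Mean lag (weeks) | More than 2 weeks | More than 4 weeks |
|---|---|---|---|---|
| 3 | 46/3 = 15.3 | 7.7 | 1 − 6/46 = 87% | 1 − 12/46 = 74% |
| 4 | 46/4 = 11.5 | 5.8 | 1 − 8/46 = 83% | 1 − 16/46 = 65% |
| 5 | 46/5 = 9.2 | 4.6 | 1 − 10/46 = 78% | 1 − 20/46 = 57% |

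So 13% to 22% of onsets fall within 2 weeks after a draw, and 26% to 43% within 4 weeks.

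**Step 2: sensitivity to placement.** If one draw falls at season end it precedes no recorded onset, and k − 1 replaces k. For 3, 4 and 5 draws the shares become 91%, 87% and 83% beyond 2 weeks, and 83%, 74% and 65% beyond 4 weeks.

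**Step 3: what the single label does.** Take three evenly spaced draws, at weeks 0, 15.3 and 30.7, and a player whose only problem starts in week 30. His draws lie 30 weeks before, 14.7 weeks before and 0.7 weeks after the onset. The ANOVA treats all three as values of an injured player.

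**Step 4: what can still be estimated.** With no missed draws there are 149 × 3 = 447 to 200 × 5 = 1000 samples. At 20% to 45% prevalence, about 447 × 0.20 = 89 to 1000 × 0.45 = 450 of them are taken while a problem is present. At one visit with 200 players, the difference detectable with 80% power (two-sided 5%) is (1.96 + 0.84) × √(1/40 + 1/160) = 0.50 SD at 20% prevalence, and (1.96 + 0.84) × √(1/90 + 1/110) = 0.40 SD at 45%. Concurrent association is within reach.

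**Step 5: onsets left for a 4-week window.** N × k × 4 × incidence runs from 149 × 3 × 4 × 0.02 = 36 to 200 × 5 × 4 × 0.10 = 400. Keeping only players without a problem at the draw (55% to 80% of them, from the same prevalences) leaves about 36 × 0.55 = 20 to 400 × 0.80 = 320, if incidence is the same in those players. The range is wide because the article gives no incidence.

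**The case against.** A reader might infer that the sampling schedule leaves the secondary aim unanswerable. The documents do not support that. The aim also covers stress and load, which can be matched to the questionnaire of the same week at every draw. For injury and illness, concurrent association, period-level differences and the minority of onsets soon after a draw can all be estimated (step 4).

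A reader might also infer that some players get five draws and others three. The text does not say so; the range can be read as the number of study-level timepoints. Nor can it be said that the sampling dates are missing: Figure 1 is the assessment plan, is not shown here, and may give them.

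Three further objections deserve weight.
- The regressions are not stated to be period-level, and onset is known to the week, so a time-ordered link is possible with the planned data. That is true, but the article states none, while for the ANOVA it does state a grouping that rules time order out. The defect therefore lies in what is specified, not only in detail that a fuller document might add.
- The percentages rest on even spacing, whereas draws follow the training cycle. The figures are illustrations. The direction holds unless onsets cluster just after draws, which nothing in the text suggests.
- Nothing in the article says how long a biomarker value stays informative. If the signal is slow, the loss from long lags is smaller. That weakens the dilution argument but does not touch the mixing of draws before and after onset.

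**Conclusion.** The concern holds for prediction and short-lead monitoring of onset, not for the whole secondary aim. As specified, the ANOVA combines draws before and after the event under one label, and the ROC cut-offs have no stated time horizon. With three to five draws in 46 weeks, 57% to 74% of onsets would start more than 4 weeks after the latest draw, or 65% to 83% if one draw falls at season end. These shares assume evenly spaced draws and evenly spread onsets. The fault in the grouping depends on neither assumption. The matter concerns a secondary aim and can be corrected in the analysis.

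**What to change.** No extra blood draws are needed. In the Statistical analysis section:

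1. For the predictive and ROC analyses, make the player-draw the unit. The outcome is a new health problem starting within one window after that draw, fixed before the data are seen (for example 4 weeks, which is a choice without a source in the article), with a sensitivity analysis of other lengths. Include only players without a current problem at the draw, and use a repeated-measures logistic model that accounts for dependence within a player.
2. Derive cut-offs only from that analysis and report each with its time horizon.
3. Analyse samples taken during a current problem separately, as concurrent association, so that they are not lost.
4. Describe the injured/ill versus healthy comparison by season period as descriptive association, not as prediction or monitoring of onset, and word the aim to match.

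The cost is rewording and some programming with data already planned. Fewer onsets enter the predictive analysis: under the even-spread assumptions a 4-week window leaves out 57% to 74% of them, and the restriction to players free of a problem removes more. At the low end of the assumed incidence only about 20 onsets may remain, too few for a stable cut-off. The claim becomes narrower, but it is one the data can carry.
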